### Follow-up lab visits

At the post-intervention visit after completing the last mindful walking session at week 12, participants in both groups meet with the research staff to complete in-lab assessments that are identical to the baseline measures (except the demographics surveys). Participants in both groups also meet with the research staff for two follow-up in-lab assessments after 18 and 24 weeks to evaluate the longer-term intervention effects. On the last visit, participants can provide their feedback on the study, and they will receive monetary compensation based on their compliance (up to $200).

### Measures

Participants in both groups completed identical lab-based measures at four time points (baseline, after 12 weeks, after 18 weeks, and after 24 weeks). They also conducted four measurement bursts (repeated assessments delivered multiple times per day for several days) of ecological momentary assessment (EMA) right after the four lab visits to understand how the study outcomes differ between the groups in real-life settings in short- and longer- terms. Trained research staff instruct participants on completing these in-lab and EMA measures during the lab visits. The measures and their administration timing are summarized in Table 2.

**Table 2 Tab2:** Summary of study outcomes, measurement occasions, and validated tools

Measures	Format	Administration Timing	Tools
**Primary Outcomes**			
Cognitive function	In lab	Baseline, 12,18,24 weeks	MoCA, CERAD
	Mobile	Baseline, 19, 25 weeks (4 days each)	M2C2 Mobile application
		Weeks 12 and 13 (14 days)	
**Secondary Outcomes**			
Quality of life	In lab	Baseline, 12,18,24 weeks	EQ-5D-5 L
Physical activity	In lab	Baseline, 12,18,24 weeks	CHAMPS
	Mobile	Weeks 12 and 13 (14 days)	ActivPAL accelerometer
Mindfulness	In lab	Baseline, 12,18,24 weeks	FFMQ, MAAS
Overall health status	In lab	Baseline, 12,18,24 weeks	SF-36
Mobility and gait speed	In lab	Baseline, 12,18,24 weeks	10-meter walk test
Perceived stress	In lab	Baseline, 12,18,24 weeks	PSS-10
Depressive symptoms	In lab	Baseline, 12,18,24 weeks	CES-D
Sleep quality	In lab	Baseline, 12,18,24 weeks	PSQI
**Other Covariates**			
Demographics	In lab	Baseline	Survey questions
Height and weight	In lab	Baseline	PhenX Toolkit
Body Mass Index (BMI)	In lab	Baseline	Calculated (= kg/m^2^)
Waist circumference	In lab	Baseline	PhenX Toolkit
Blood pressure	In lab	Baseline	PhenX Toolkit
Health literacy	In lab	Baseline	Validated survey item
Grip strength	In lab	Baseline	PhenX Toolkit
Daily functioning	In lab	Baseline	IADL
Social support	In lab	Baseline	PSSS
Medication use	In lab	Baseline	Survey questions

Note: MoCA: Montreal Cognitive Assessment; CERAD: Consortium to Establish a Registry for Alzheimer’s Disease subjective cognitive decline scale; M2C2: Mobile Monitoring of Cognitive Change app; EQ-5D-5L: EuroQol 5 dimensions and 5 levels of response quality of life survey; CHAMPS: Community Health Activities Model Program for Seniors physical activity questionnaire; FFMQ: Five Facet Mindfulness Questionnaire; MAAS: Mindfulness Attention Awareness Scale; SF-36: 36-Item Short Form Health Survey; PSS-10: 10-item Perceived Stress Scale; CES-D: Center for Epidemiological Studies-Depression Scale; PSQI: Pittsburgh Sleep Quality Index; IADL: Instrumental Activities of Daily Living Scale; PSSS: Perceived Social Support Scale

### Demographics, Anthropometrics, and individual characteristics

Participants self-report their demographics (age, sex, race, education level, household composition, and marital status) during the baseline lab visit. The research staff measures participants’ height and weight (for BMI calculation), waist circumference, blood pressure, and grip strength in duplicate using the PhenX Toolkit protocol in all lab visits [51]. In addition, four validated self-report measures are included in each lab visit, including: (1) Instrumental Activities of Daily Living Scale (IADL) measures participants’ independence and functioning in daily activities [52], (2) Perceived Social Support Scale (PSSS) measures participants’ perceived social support [53], (3). the types of medications currently taken, comorbidities (Charlson et al., 1994), and (4) and health literacy using one valid item [54]. All self-report data are collected via the Qualtrics online survey platform. These baseline measures serve as covariates in our analysis to adjust for individual differences at enrollment that may contribute to the study outcomes.

### Primary outcome: Multimodal measures of Cognition

The current literature has not established the specific cognitive domains that are most responsive to mindful walking interventions. Thus, this study applied both in-lab and mobile-based cognitive measures (performance-based and subjective ratings) to broadly assess cognitive health outcomes and compare results between different modes of measures. This approach provided more elaborate data regarding which cognitive domains may be more sensitive to mindful walking engagement. If positive results are observed across all cognitive measures, it will also demonstrate convergent evidence of mindful walking for sustaining cognitive health broadly [55].

***In-lab cognitive assessment***. During each lab visit, a certified research staff administers the Montreal Cognitive Assessment (MoCA) and the subjective cognitive decline scale from the Consortium to Establish a Registry for Alzheimer’s Disease (CERAD) to assess participants’ cognitive function. The MoCA is a sensitive neuropsychological measure for differentiating individuals with normal cognitive aging from those with mild cognitive decline [56]. It aggregates subscales from different cognitive domains (visuospatial/executive function, naming, memory, attention, language, abstraction, delayed recall, orientation) with a total maximum score of 30. A cutoff score of 26 on MoCA at baseline is used for the block randomization to ensure participants are comparable in baseline cognition between the two groups [56]. The alternate forms of MoCA (v8.1 to v8.3) are applied for each measurement occasion to minimize potential learning effects [57]. The CERAD cognitive decline scale is also a valid tool that can detect the occurrence of early cognitive deficits before other cognitive tests can capture them during the ADRD preclinical stage [58, 59].

***Mobile cognitive assessment.*** This study applies ultra-brief smartphone-based cognitive tests from the NIH-funded M2C2 (Mobile Monitoring of Cognitive Change) application platform to measure participants’ cognitive function in naturalistic settings during four intensive measurement bursts [60, 61]. The first burst lasts for four days after the initial lab visit to establish participants’ baseline everyday cognitive function. The second burst is scheduled for 14 days from weeks 12 to 13. The weeks 12 measures overlap with the last two sessions of mindful walking, reflecting the cognitive function changes during the intervention period for the intervention group. We include the week-12 measures to understand whether participants’ cognitive function differs with and without the mindful walking intervention exposure (as a secondary analysis). However, the short-term efficacy of everyday cognition will be evaluated using the data collected in weeks 13 after the intervention group completes all the walking sessions. The third and the fourth bursts are scheduled right after the 18-week and after the 24-week lab visits, respectively. These longer-term measurement bursts will determine if there are sustained intervention effects.

During each measurement burst, the M2C2 app delivers four semi-random daily notifications during waking hours. Upon hearing a notification, participants use the smartphone touch screen to complete three ultra-brief cognitive tests in everyday contexts. The three brief cognitive tests include the symbol search (targeting mental processing speed), the grid memory (targeting visuospatial working memory), and the color shapes (targeting executive function). These validated cognitive tests are selected due to their sensitivity to the cognitive domains influenced by lifestyle behaviors, cognitive aging, and age-related neuropathology [62, 63]. Participants are asked to ignore prompts delivered during an incompatible activity (e.g., driving, cooking, biking) for safety purposes.

In the Symbol Search test, participants select a combination of symbols from the bottom of the screen that matched the one presented at the top of the screen as fast as they can. In the Grid Memory task, participants need to recall the locations of three red dots that appeared during the previous brief study phase. A distraction page (a letter cancellation task) is embedded between the study and the test phase. In the Color Shapes test, participants determine whether the combination of colors and shapes is identical among three visual objects (distributed throughout the array) between the study and test arrays. This cognitive test is highly sensitive to early subtle cognitive changes in the presence of ADRD pathology prior to formal detection from standard neuropsychological tests [64]. Each day, participants encounter different test stimuli for each brief cognitive test at each EMA notification.

The primary outcome of the Symbol Search test is the median response time (RT) for the accurate trials; the primary outcome of the Grid Memory test is the mean error distance of the dots between the study and test phases; the primary outcome of the Color Shapes test is the corrected recognition rate (i.e., the hitrate minus the false alarmrate). In our pilot testing in older adults, participants can complete the three ultra-brief cognitive tests within a total of 5 min (18 trials for Symbol Search, 3 trials for Grid Memory, and 12 trials for Color Shapes).

### Secondary outcomes

The secondary outcomes are self-reported quality of life, overall health status, physical activity, perceived stress, depressive symptoms, mindfulness, and sleep quality. We use the EQ-5D-5L survey to measure participants’ health-related quality of life (HRQOL) at baseline, 12, 18, and 24 weeks. The EQ-5D-5 L is easy to administer and is the most widely used instrument to measure HRQOL among individuals with predementia or mild cognitive decline [65]. The EQ-5D-5 L includes both the negative aspects (illness) and the positive aspects (well-being) that are highly associated with older adults’ ability to function independently, mortality rate, and hospitalization occurrence in the long term [66, 67].

The SF-36 Short-form Health Status Questionnaire assesses participants’ overall physical and mental health [68]. The Community Health Activities Model Program for Seniors questionnaire (CHAMPS) assesses participants’ overall physical activity levels [69, 70]. The Mindfulness Attention Awareness Scale (MAAS) and the Five Facet Mindfulness Questionnaire (FFMQ) assess participants’ trait mindfulness levels. These two mindfulness scales are the most common tools applied in physical activity research [71, 72]. The 10-item Perceived Stress Scale (PSS-10) will assess participants’ overall stress levels [73, 74]. The Center for Epidemiological Studies-Depression Scale (CES-D) assesses participants’ depressive symptoms [75]. The Pittsburgh Sleep Quality Index (PSQI;18 items) measures participants’ sleep quality [76]. The 10-meter walk test will assess participants walking speed (meters/sec) over a short distance to determine their functional mobility and gait speed against the age-based normative values [77].

**Device-based measure of daily movement activity.**

This study applied the research-grade activPAL accelerometer (PAL Technologies, Glasgow, UK) to measure physical activity outcomes in both groups during the four measurement bursts that overlap with the mobile cognitive assessment period. ActivPAL is a valid and reliable accelerometer to capture subtle changes in posture (e.g., sitting, standing) and movement (e.g., stepping) among older adults in free-living contexts [78–80]. During each measurement burst, participants wear the activPAL on the thigh for 24 h a day, including sleep time but excluding bathing or swimming time. A copy of the activPAL wearing instructions is provided to participants at their baseline visit.

In the activPAL output file, accumulated steps and minutes of light, moderate, and vigorous physical activity are summarized across all waking hours for each wear day [81]. In this study, the time spent in different intensities of physical activity (i.e., light, moderate, or vigorous) is determined by the activPAL ActivityScore (MET.h) value (a proxy index of energy expenditure levels) with reference to the CDC metabolic equivalents (METs) cutoff values [82]. This device-based data compares physical activity levels (and steps) between the two groups before, during, and after the mindful walking intervention.

### Adherence plan

Participants can decide to drop out of the study at any time without providing a reason, and there are no consequences if they quit the study. A variety of strategies are employed to promote intervention adherence, measurement completion, and study retention. The research team strives to establish a positive rapport with participants and provides responsive support throughout the study period. Prior to enrollment, the staff outlines the potential pros and cons of study participation to let participants make an informed decision about participating and the expectations [83]. The weekly check-in phone calls and text messages conducted during the intervention period also encourage participants to comply with the study protocol. The staff delivers reminder texts or emails to each participant for their upcoming walking sessions and lab visits. During the baseline lab visit, participants should identify two secondary contacts in case the study team can not reach the participant. We offer flexible scheduling to accommodate participants’ time for the walking sessions and visits, including walking on weekend days.

In addition, financial incentives are provided after participants complete the in-person measures and the activity monitoring. Participants receive up to $200 if they complete the entire study with proper compliance (complete all in-lab measures and provide ≥ 70% of the EMA and activPAL data). Specifically, they receive $25 for completing the baseline and the-12 week measures, $60 for completing the 14-day EMA monitoring, $35 for the 18-week measures, and $40 for the 24-week measures. Participants who complete the entire study protocol with ≥ 70% compliance rate are eligible to participate in a drawing to earn an extra $40. Lastly, participants will receive a summary of their physical activity levels during the monitoring period collected by the activPAL device.

### Data preparation, analysis, and management

***Power and sample size consideration***. We conduct apriori power and sample size calculation to detect at least a small between-group effect (Cohen’s *d* = 0.2) based on the available literature showing the anticipated effect sizes from mindfulness-based physical activity programs and cognitive health in older adults [84–86]. The power analysis R package “powerlmm” is used to determine the sample size in the mixed-effects analysis framework with repeated measures. The package identified that a total sample size of 114 participants (57 in each group) would support the detection of the pre-specified small effect size between two groups with sufficient power (≥ 0.80) [87]. We plan for a 15% dropout rate based on the attrition rate in our preliminary study and the annual injury rates (~ 5%) in older adults (i.e., due to serious falls) that lead to unanticipated dropouts [88]. Thus, we will recruit 18 extra participants to account for the attrition, so the actual power for analysis is likely to be greater.

***Statistical analysis***. After the study is completed, we will first examine the distributions of all the quantitative outcome variables prior to any statistical analysis. If any variables violate the normal distribution assumption, we will apply proper sampling distributions and link functions to model the data [89]. We will apply the generalized linear mixed-effects modeling to examine the short- and longer-term effects of mindful walking on cognition and other study outcomes. The repeated measures collected across the study period are the within-subject components, and the group allocation (mindful walking vs. delayed walking group) is the between-subject component in the model. The primary interest in the model is the Time x Group interaction term, which will determine whether significant differences exist in the outcomes between the two groups from baseline to post-intervention. The analyses will be conducted in R program version 4.0.1 [90]. Participants’ baseline characteristics and demographics (e.g., sex, age, BMI, general health status, etc.) will be adjusted in all models. We will also control for participants’ enrollment time of the year (in months) in our analyses to account for any potential seasonal effects that may impact the study outcomes.

***Missing data handling***. The study team minimizes missing data through rigorous staff training before data collection and regular contacts with participants to ensure compliance. We will conduct missing pattern analysis and take relevant measures to reduce missing data-related bias in our analytic models. For example, we will run suggested expectation-maximization imputation methods to compare model results with and without data imputation [91–93]. The analyses of all the study outcomes will be conducted following the intention-to-treat principle [94].

***Data management***. All data collected, including personal information (demographics) from this study will be stored and saved on password-protected and encrypted servers at the university to ensure data safety. No personal information about the screened and enrolled participants will be shared beyond the research team to protect confidentiality. Any published data and articles from this study will be de-identified to exclude any personal information. One graduate-level research assistant is designated to conduct weekly checks of the collected data to promote data quality and identify any errors in data entry, coding, storage, or data uploading.

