**Methods:**

This paper documents the goal and protocol of a community-based, mindful walking randomized controlled trial to examine the short- and longer-term efficacy on cognitive and other health-related outcomes in ADRD at-risk AA older adults. The study outcomes include various brain health determinants, including cognitive function, quality of life, psychological well-being, physical activity, mindfulness, sleep, and overall health status. In addition, the estimated costs of program implementation are also collected throughout the study period. This study will recruit 114 older adults (ages 60+ years) with elevated ADRD risk from the Midlands region of South Carolina. Older adults are randomly assigned to participate in 24 sessions of outdoor mindful walking over three months or a delayed mindful walking group (*n*=57 in each group). Participants in both groups follow identical measurement protocols at baseline, after 12 weeks, after 18 weeks, and after 24 weeks from baseline. The outcome measures are administered in the lab and in everyday settings. Costs per participant are calculated using micro-costing methods. The eliciting participant costs for mindful walking engagement with expected results are reported using the payer and the societal perspectives.

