### Participants

This study will recruit a total of 114 gender-inclusive older AA adults aged 60 and above in the Midlands region of SC. Instead of using the typical age 65 cutoff for older adults, the age of 60 is selected because this study is designed to inform risk-reductive behavioral strategies to sustain cognitive health during the early preclinical stage of ADRD. Our inclusion and exclusion criteria, as outlined below, also seek to make this program available to most AA older adults who have increased risks for developing ADRD (e.g., does not require prominent levels of physical capacity and mobility), and thus, may benefit from participating in mindful walking.

The inclusion criteria included: (1) African American older adults age 60 and above, (2) have at least one ADRD risk factor (including experiencing subjective cognitive decline or memory complaints, having a family history of ADRD, being physically inactive at enrollment based on the 2018 Physical Activity Guidelines for Americans, having higher BMI (≥ 25)), (3) have adequate hearing and visual ability to complete study tasks and assessments, (4) English proficiency, (5) be medically stable with or without medication, (6) be able to provide informed consent, and (7) be willing to be randomized to one of the two groups. The exclusion criteria included: (1) have a clinical diagnosis of ADRD or other brain abnormalities (e.g., strokes, epilepsy, Parkinson’s disease), (2) have a clinical diagnosis of a psychiatric disorder (i.e., major depression, post-traumatic stress disorder, bipolar disorder), (3) unable to walk independently (i.e., need caregiver’s assist), (4) plan to have surgery or relocate outside the area within the next 12 months, and (5) currently participate in other study involving physical activity, mindfulness or meditation, or cognitive training. We selected these exclusion criteria to ensure that older adults have the capacity to carry out the study protocol and that their current health condition will not bias or interfere with the study outcomes.

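### The recruitment total is 114 in two places, but the power paragraph implies 132; the promise of greater power is wrong for 114 and unsupported for 132

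*Protocol article*

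**What the plan says.** Three places in the protocol article bear on the recruitment number.

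- Abstract, Methods: "This study will recruit 114 older adults (ages 60+ years) with elevated ADRD risk", allocated as 57 per group.
- Participants: "This study will recruit a total of 114 gender-inclusive older AA adults aged 60 and above".
- Data preparation, analysis, and management, paragraph on power and sample size: the powerlmm package is credited with this result: "a total sample size of 114 participants (57 in each group) would support the detection of the pre-specified small effect size between two groups". The stated power is at least 0.80 for Cohen's d = 0.2. The paragraph continues: "We plan for a 15% dropout rate based on the attrition rate in our preliminary study", together with an annual injury rate of about 5%. It ends: "we will recruit 18 extra participants to account for the attrition, so the actual power for analysis is likely to be greater".

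No total of 132, and no group size of 66, appears anywhere. The text does not say whether the 18 are already inside the 114.

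**The concern.** The same figure, 114 (57 per group), is both the number to be recruited and the number the power calculation needs before any loss. Both cannot hold if 18 further participants are recruited because of dropout. In the order in which the power paragraph argues (requirement, then dropout, then extra recruits), the total is 132, and the Abstract and Participants section are wrong. If those two sections are right, the attrition allowance does not exist and the stated power assumes that nobody leaves.

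The closing clause adds to the problem. Recruits added to offset an expected loss are there to restore the planned power, and the paragraph gives no other reason to expect more. According to the Trial status section, recruitment was still under way when the article was submitted, so the number at which to stop enrolment was a live question.

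**Working it through.** **Inputs from the power paragraph:** 114 required (57 per group), power at least 0.80, 15% dropout, 18 extra.

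**Assumptions (not in the article):** two-sided alpha of 0.05; power of exactly 0.80 at 114 with no dropout, since dropout enters the text only after the 114. For the mixed model: four visits (baseline, 12, 18 and 24 weeks), compound symmetry with correlation 0.5, 0.7 or 0.9, and monotone 15% dropout, either spread evenly (5% after each of the first three visits) or all before week 12.

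**Step 1. Reproduce the 18.** 114 × 0.15 = 17.1, rounded up to 18. Per group, 57 × 0.15 = 8.55, rounded up to 9, and 2 × 9 = 18. The article shows no formula, so this origin is inferred.

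**Step 2. Implied total.** 114 + 18 = 132 (66 per group), against 114 in the Abstract and Participants section.

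**Step 3. Expected completers at 15% loss.**
- 114 recruited: 114 × 0.85 = 96.9.
- 132 recruited: 132 × 0.85 = 112.2.
- To keep 114 completers: 114/0.85 = 134.1, so 135, or 136 for equal groups (2 × 68). That is 21 or 22 extra rather than 18.
- 132 recruits leave 114 or more completers only if dropout is at most 1 − 114/132 = 13.6%.

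**Step 4. Power counting completers only.** Power = Φ(2.802 × √(N/114) − 1.960), where 2.802 = 1.960 + 0.842.
- N = 96.9: √0.85 = 0.922, and Φ(0.623) = 0.733.
- N = 112.2: √0.984 = 0.992, and Φ(0.820) = 0.794.

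**Step 5. Power when the mixed model keeps partial data.** The effective N for the group difference in change from baseline replaces N in the same formula.

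| Randomised | Completers | Power, completers only | Effective N, mixed model | Power, mixed model |
|---|---|---|---|---|
| 114 | 96.9 | 0.733 | 97.6 to 109.7 | 0.737 to 0.785 |
| 132 | 112.2 | 0.794 | 113.0 to 127.0 | 0.797 to 0.841 |

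For 132 randomised, evenly spread dropout gives 0.837 to 0.841 at week 12 and 0.807 to 0.813 at week 24. Dropout entirely before week 12 gives 0.797 to 0.809.

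**The case against.** A reader might infer that the power sentence is false whichever total applies. The article does not support that. It plans a mixed model on repeated measures under intention-to-treat, so people who leave after week 12 or week 18 still contribute. With 132 randomised, most scenarios above lie slightly over 0.80, and power would also exceed the plan if dropout stayed below 13.6%. The sentence is hedged as likely. For 132 this objection stands: the clause lacks support but has not been shown false.

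A reader might also infer that the inflation was done by the wrong formula. That is only an inference from the size of the 18. The figures equally fit a correct inflation from 96: 48/0.85 = 56.5, rounded up to 57 per group, so 114 in total, and 114 − 96 = 18. On that reading 96.9 completers would give power of about 0.804, and the Abstract and Participants section would be right. However, the article credits 114 to the package, and 96 appears nowhere, so the power paragraph would then need correcting. Even if the 18 is simply 15% of 114, the shortfall is about 2 completers, or 0.6 percentage points of power.

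It is also possible that the package run already allowed for dropout. In that case 114 recruits would hold 0.80 and 18 more would raise it. The paragraph does not say so, and it introduces dropout only after the 114.

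Finally, one could express the loss as a larger detectable effect from a plain two-sample comparison. That is not the planned analysis and should not be used to size this point.

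**Conclusion.** The point holds. The article gives two incompatible recruitment totals, 114 and an implied 132, and every reading requires some sentence to change.

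- **If 114 is recruited against a requirement of 114:** there is no attrition allowance, about 97 complete, and power is about 0.73 on completers or about 0.74 to 0.785 with partial data. The clause promising greater power points the wrong way.
- **If 132 is recruited:** about 112 complete and power is about 0.79 to 0.84. The clause is unsupported. The allowance of 18 is 3 or 4 recruits short of what would keep 114 completers, which is minor.

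These figures take the article's 0.80 at 114 as given and rest on the assumed alpha, correlation structure and dropout timing. The powerlmm inputs are not stated, so the 114 could not be reproduced, and whether it supports d = 0.2 is a separate question.

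**What to change.** 1. State one recruitment total, with matching group sizes, in the Abstract, the Participants section and the power paragraph.
2. Say whether 114 is before or after the attrition allowance. If 114 must remain after 15% loss, show the inflation as N/(1 − dropout): 135, or 136 for equal groups.
3. For the chosen total, give the expected number of completers and the power at 15% dropout, with all randomised participants kept in the intention-to-treat mixed model and the assumptions listed.
4. Delete the clause about greater power, or justify it with that calculation.

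**Cost.** If 114 stands, only figures are restated: no extra participants are required, but the stated power becomes slightly less favourable. If 132 is meant, the Abstract and Participants section change to 132 (66 per group), and the 18 extra people are those the power paragraph already promises. Moving to 135 or 136 would add 3 or 4 recruits to that.

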#### Randomization

After completing the baseline measures, participants are randomly assigned to the mindful walking group, or the delayed mindful walking group based on block randomization by the staff. Random blocks were generated by a methodologist on the team, stratified by sex (male vs. female) and baseline cognitive function (normal cognition vs. mild cognitive decline based on MoCA; see Measures section) to balance the two groups. The rest of the research team is blinded to the condition allocation sequence kept in sealed envelopes. Participants assigned to the intervention group schedule their 24 mindful walking sessions with the staff from week 1 to week 12. Participants assigned to the delayed mindful walking group are asked to live their normal lives and follow their regular daily routines without changing their behaviors until they start their mindful walking sessions after week 24. The measurement schedule is identical between the two groups from baseline to the last follow-up to compare group differences with or without the intervention.

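### As worded, the primary Time x Group model leaves the arms' baseline means free and adjusts for season with enrolment month, which cancels from the interaction; both cost precision, not validity

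*Protocol article*

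**What the plan says.** All of this is in the protocol article.

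- **Primary contrast** (Data preparation, analysis, and management; Statistical analysis): "The primary interest in the model is the Time x Group interaction term, which will determine whether significant differences exist in the outcomes". The comparison runs from baseline to after the intervention, and "the group allocation (mindful walking vs. delayed walking group) is the between-subject component in the model".
- **Visits** (Measures): lab outcomes are taken "at four time points (baseline, after 12 weeks, after 18 weeks, and after 24 weeks". Baseline is therefore one of the repeated responses.
- **Effects of interest** (Methods, paragraph after Figure 1): the short-term effect is the group difference between baseline and 12 weeks. The longer-term effect covers baseline to 18 weeks and baseline to 24 weeks.
- **Covariates** (Statistical analysis): "baseline characteristics and demographics (e.g., sex, age, BMI, general health status, etc.) will be adjusted in all models". The section on demographics and anthropometrics adds: "These baseline measures serve as covariates in our analysis to adjust for individual differences at enrollment".
- **Season** (Statistical analysis): the analyses will control for "enrollment time of the year (in months) in our analyses to account for any potential seasonal effects that may impact the study outcomes".
- **Randomisation**: blocks are "stratified by sex (male vs. female) and baseline cognitive function", with a MoCA cut-off of 26.

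No model formula is written out. Neither an equal-baseline constraint nor the baseline outcome as a covariate is mentioned.

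**The concern.** Two choices work against the precision of a trial with 57 participants per arm.

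First, when baseline is a response and each arm has its own baseline mean, the Time x Group effect at week 12 is the difference between arms in mean change. Randomisation makes the true baseline means equal. A model that uses this fact, or that adjusts for the baseline outcome, estimates the same effect with a smaller variance.

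Second, enrolment month is constant within a participant. Enrolment is rolling and follow-up lasts 24 weeks, so the season changes between a participant's baseline and later visits by an amount that depends on when they enrolled. A main effect of enrolment month shifts all of a participant's visits equally and cannot describe that change. For an outdoor walking programme, the stated seasonal control then does not act on the contrast that matters.

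**Working it through.** **Plan's own figure.** The article gives no variance for this contrast. The nearest figure is 114 participants (57 per arm) for d = 0.2 with power of at least 0.80. It cannot be reproduced, because no within-person correlation or alpha is stated. Assuming two-sided 0.05 and SD 1, a comparison at follow-up alone needs 393 per arm, and 57 per arm gives power 0.186. For power 0.80 at 57 per arm the variance factor must be 57 x 0.2² / (2 x (1.960 + 0.842)²) = 0.145. For a change contrast that means 2(1 - rho) = 0.145, so rho is about 0.927. This is used below as the upper end of the range.

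**Step 1: free versus constrained baseline.** With SD 1, complete data and n per arm, the variance of the week-12 contrast is 2/n times:

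- free baseline means (change contrast): 2(1 - rho)
- common baseline mean, or baseline-adjusted: 1 - rho²

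Constrained over free is (1 - rho²) / (2(1 - rho)) = (1 + rho)/2. The free model's variance is therefore 2/(1 + rho) times the constrained one.

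| rho (assumed) | free | constrained | ratio | reduction | power, free | power, constrained |
|---|---|---|---|---|---|---|
| 0.5 | 1.00 | 0.75 | 0.75 | 25% | 0.186 | 0.234 |
| 0.7 | 0.60 | 0.51 | 0.85 | 15% | 0.280 | 0.321 |
| 0.9 | 0.20 | 0.19 | 0.95 | 5% | 0.665 | 0.688 |
| 0.925 | 0.15 | 0.144 | 0.963 | 3.7% | 0.787 | 0.802 |

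The power columns use 57 per arm, d = 0.2 and two-sided 0.05. At rho 0.927 the reduction is (1 - 0.927)/2 = 3.7%, to one decimal. In participants, the constrained model would match the free model at 57 per arm with 57 x 0.75 = 43 per arm (rho 0.5), 57 x 0.85 = 48 (0.7) or 57 x 0.95 = 54 (0.9).

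**Step 2: check by generalised least squares.** Simulated data with 57 per arm and four visits:

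- Compound symmetry 0.7: week-12 SE 0.1451 free, 0.1338 constrained. By formula, sqrt(2 x 0.60/57) = 0.1451 and sqrt(2 x 0.51/57) = 0.1338.
- Autoregressive 0.8 between adjacent visits: week-12 SE 0.1185 free, 0.1124 constrained. At week 24 it is 0.1851 free, 0.1609 constrained. There the correlation with baseline is 0.8³ = 0.512, and (1 + 0.512)/2 = 0.756. The gain grows as correlation with baseline fades.

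**Step 3: enrolment month.** Write a participant's outcome at visit t as m_t + (group effect at t) + c + error, where c is the effect of enrolment month and does not depend on t. The week-12 change is (m_12 - m_0) + (group effect at 12 - group effect at 0) + error difference, so c has gone. In the same simulation, 11 month indicators and a stratum main effect were added to the free-baseline model. Under compound symmetry the three interaction estimates stayed at 0.13165, 0.22677 and 0.20971, each with SE 0.1451, unchanged to five decimals. The invariance also held under the autoregressive covariance. The same algebra applies to sex, age and BMI as main effects.

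**The case against.** The article condenses a fuller plan and shows no formula, so baseline handling, time coding and the way covariates enter may all be settled elsewhere. A Time x Group mixed model with free baseline means is also valid and unbiased under randomisation; preferring another is a matter of efficiency. Both points stand, and they limit the finding to the natural reading of what is written. They do not remove it, because the article itself names the interaction as the primary interest and enrolment month as the seasonal control.

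Enrolment month could be crossed with visit. Because visits fall at fixed weeks in both arms, that would carry season approximately. This is fair and is accepted below as an alternative, but the article does not say it. Cancellation is exact only with complete visits and an identity link, whereas the plan allows for 15% dropout and other link functions. With those, the month term would have some effect, but it still could not represent within-person seasonal change.

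Four stronger readings are tempting and are not supported:

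- **A 15 to 25% loss as a fact.** That range holds only for rho 0.5 to 0.7, and the article states no rho.
- **Lost precision because the MoCA stratum is unnamed.** The covariate list is open-ended, so unnamed is not excluded. A stratum main effect would also cancel from the free-baseline interaction, so its absence costs nothing in that model.
- **A single linear time trend.** The article does not say time is linear, and its visit-by-visit definition of the short- and longer-term effects points the other way.
- **Seasonal bias.** Both arms are randomised from the same rolling enrolment on the same visit schedule, so season is balanced in expectation. The size of the precision loss is unknown; a simulated fall in SE from 0.172 to 0.139 with date-based terms came from one dataset with an assumed 0.5 SD swing.

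**Conclusion.** The point holds as a matter of efficiency and of a stated adjustment that does not do its job. On the natural reading, constraining the baseline would reduce the variance of the week-12 contrast by 25% at rho 0.5, 15% at 0.7, 5% at 0.9 and under 4% near 0.93, the correlation that the stated power would need. In power at d = 0.2 this is about 5 points at rho 0.5 (0.186 to 0.234), about 4 at 0.7 and 1.5 near 0.925. These figures assume equal variances across visits, complete data, an identity link and two-sided 0.05.

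Enrolment month as a main effect gives no seasonal control of the primary contrast under complete data and an identity link. The consequence is lost precision of unknown size. Neither issue makes the planned test invalid.

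**What to change.** Before outcomes are examined by arm, state the primary model in full:

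1. Fit visit as a four-level factor with one baseline mean common to both arms, or adjust for the baseline outcome.
2. Pre-specify group contrasts at weeks 12, 18 and 24, matching the article's own definitions of short- and longer-term effects.
3. Include both randomisation strata, sex and MoCA stratum, each with its visit interaction. For MoCA as the outcome, the stratum is a cut of the baseline response itself, so the baseline-adjusted form is the cleaner choice there.
4. Replace enrolment month with seasonal terms, such as sine and cosine, based on each assessment's calendar date. A month-by-visit term is the alternative, but 11 month indicators crossed with three follow-up visits add 33 parameters, against two for one sine-cosine pair.

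The cost is wording and a few degrees of freedom: the two strata with visit interactions take 2 x (1 + 3) = 8 parameters. The baseline outcomes and strata are already collected. Assessment dates should be available from visit scheduling, although the article does not say so.
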